### Sample Size Calculation

Based on our study population, the expected incidence of PoAF in our study population is 32% [25]. The sample size calculation of the present study design was based on dichotomous outcomes for two independent groups (treatment and placebo), as this parameter has an expected incidence drop from 32 to 12%, where alpha = 5%, beta = 0.2, and power = 80% and 2-sided testing [R Statistics 3.6.3, pwr-package 1.3–0]. Therefore, the initial required number of patients undergoing cardiac surgery is 66 in the GGA-treated group and 66 in the placebo group. An attrition rate of 10% increases this to 73 patients in the GGA-treated group and 73 in the placebo group.

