### Secondary Endpoints

All collected tissue samples will be analyzed to assess levels of HSPB1, HSPA1A, and phosphorylated HSF1, and proteostasis markers, as well as the degree of structural remodeling using (confocal) microscopic imaging.

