## Statistical Analyses

Regarding clinical characteristics from the study population, such as indication for cardiothoracic surgery, age, sex, BMI, hypertension, diabetes mellitus II, and statin intake, descriptive statistics of continuous variables will be presented as means with standard deviations (SD) or medians with interquartile ranges (IQR), depending on the distribution of the data. Categorical data will be presented as proportions and numbers.

The statistical efficacy analysis is conducted according to the intention-to-treat principle with a chi-square test for proportions of PoAF incidence until D3, between the treatment arms. All randomized patients are included in the primary endpoint analysis. We use the Cox-Mantel test in order to calculate survival rates (PoAF as outcome) until hospital discharge between treatment arms.

HSP levels are continuous measures assessed on adipose tissue and atrial tissue. Adipose and atrial tissue are collected once during surgery. Here, the comparison between control and intervention is cross-sectional, and individual measurements are independent. They will be analyzed using linear regression to compare study arms while adjusting for stratification factors (sex, age, and cardiac surgery indication). HSP levels are also continuous measures assessed on blood samples which are collected at three time points: baseline appointment, at day of surgery, and at day 3 after surgery (see Fig. 1). Therefore, we use statistics suited to longitudinal data, as these are thus dependent observations (correlated within patients). A linear mixed model with at least random intercepts, and, if required, random slopes for time and/or treatment, will be used to compare study arms while adjusting for stratification factors. To preserve the overall type I error rate over all secondary endpoints, Bonferroni correction will be used.

Values of *p* < 0.05 are considered statistically significant. SPSS version 20 (IBM Analytics), R Statistical Software (R Studio, Inc., Boston, MA, USA; version 1.0.153), and GraphPad Prism version 8.0 (GraphPad Software Inc., CA) are used for all statistical evaluations.

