### Randomisation and Blinding

For randomization, we consider a 1:1 allocation ratio. Stratified random sampling will take into consideration the following: age (18–60 years or 60–80 years old), sex (male and female), and indication for cardiothoracic surgery (valve disease, CABG, and concomitant valve disease + CABG). Therefore, 12 strata will be considered. A random block size of 4 will be considered.

Stabilization of atrial cardiomyocyte proteostasis appears to be an upcoming and promising therapeutic strategy to avert the AF onset. The GENIALITY trial is the first clinical study to investigate whether HSP-boosting therapy can clinically prevent the incidence of AF in patients undergoing cardiothoracic surgery. The study outcomes will also contribute to a better understanding of the HSP pathway under therapeutic intervention, fostering future investigations with GGA derivatives.

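### Bonferroni for the secondary endpoints is valid, but Holm's step-down procedure gives the same family-wise control and never rejects less: a cheap, minor improvement

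*Protocol article*

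**What the plan says.** Three places in the protocol article bear on this point.

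- **Statistical Analyses, multiplicity.** "To preserve the overall type I error rate over all secondary endpoints, Bonferroni correction will be used". Neither the number of tests nor the adjusted threshold is given.
- **Statistical Analyses, next paragraph.** A general sentence says that p-values below "0.05 are considered statistically significant". It does not say whether these are raw or adjusted p-values.
- **Secondary Endpoints.** Collected tissue is to be analysed for "levels of HSPB1, HSPA1A, and phosphorylated HSF1, and proteostasis markers, as well as the degree of structural remodeling". The Tissue Analysis section names the same three markers and structural remodelling, in serum, epicardial adipose tissue and atrial tissue, but does not list the further proteostasis markers.

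Power is claimed only for the primary endpoint: "alpha = 5%, beta = 0.2, and power = 80% and 2-sided testing", for an "expected incidence drop from 32 to 12" percent.

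**The concern.** Bonferroni tests every secondary hypothesis at 0.05 divided by the number of hypotheses, whatever the other results show. Holm starts at that threshold and relaxes it after each rejection, with the same guarantee. If GGA raises several heat shock proteins in several sample types at once, which is the mechanism the trial is built on, Bonferroni gives up power that could be kept at no cost in type I error.

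What is at stake is the strength of the mechanistic secondary results, not the primary comparison. A lesser matter is that anyone applying either method needs to know which tests are in the family, and two sections of the article describe it slightly differently.

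**Working it through.** **1. The plan's own figure.** The only sample size stated is for the primary endpoint: "66 in the GGA-treated group and 66 in the placebo group". For 32% against 12%, two-sided 5%, 80% power and 1:1 allocation, the pooled-variance formula gives 67 per arm. The arcsine formula (h = 0.495) gives n = 2 × ((1.960 + 0.842)/0.495)² ≈ 64.05, so 65. The stated 66 lies between these. Its power is 79.9% (pooled) or 81.2% (arcsine). The stated 73 per arm with attrition agrees with 66 × 1.10 = 72.6. None of this depends on the method used for secondary endpoints.

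**2. Inputs for the comparison.**

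| Input | Value | Source |
|---|---|---|
| Patients per arm | 66 | Sample Size Calculation |
| Family-wise level | 0.05 | Statistical Analyses |
| Number of tests m | 3 markers × 3 sample types = 9 | markers and sample types from Tissue Analysis; treating them as nine tests is an assumption |
| Standardised difference d | 0.5 SD (also 0.3 and 0.7) | assumption |
| Correlation between tests | 0.3 (also 0, 0.5, 0.8) | assumption |

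**3. Thresholds.** Bonferroni tests each p-value at 0.05/9 = 0.0056. Holm orders the p-values and compares the i-th smallest with 0.05/(9 − i + 1), stopping at the first failure: 0.0056, 0.0063, 0.0071, 0.0083, 0.0100, 0.0125, 0.0167, 0.0250, 0.0500. No Holm threshold is below 0.0056, so every Bonferroni rejection is also a Holm rejection.

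**4. Error control.** Suppose m₀ of the nine null hypotheses are true. When Holm first rejects a true one, at least m₀ hypotheses are still in play, so that p-value is at most 0.05/m₀. The chance that any of the m₀ true nulls has so small a p-value is at most m₀ × 0.05/m₀ = 0.05, under any dependence.

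**5. Bonferroni power by formula.** The noncentrality is 0.5 × √(66/2) = 2.872. The two-sided critical value at 0.0056 is 2.773. Power per test is Φ(2.872 − 2.773) = Φ(0.099) = 0.54.

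**6. Holm power by simulation.** I used equicorrelated normal test statistics. Average power is taken over the endpoints that truly respond.

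| d (SD) | Endpoints responding | Correlation | Bonferroni | Holm |
|---|---|---|---|---|
| 0.5 | 9 of 9 | 0.3 | 54% | 65–66% |
| 0.5 | 3 of 9 | 0.3 | 54% | 56% |
| 0.5 | 1 of 9 | 0.3 | 54% | 54% |
| 0.3 | 9 of 9 | 0.3 | 15% | 17% |
| 0.7 | 9 of 9 | 0.3 | 89% | 96% |

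Before rounding, the gain with all nine responding is about 2 to 3 points at d = 0.3 and about 7 points at d = 0.7. At d = 0.5 with all nine responding, Holm's average power stays at about 64–66% for correlations from 0 to 0.8.

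**7. Dependence on m.** The Bonferroni threshold is 0.0167 for 3 tests, 0.0056 for 9 and 0.0025 for 20, so the content of the family does matter when the rule is applied.

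**The case against.** The strongest objection is that nothing here is wrong. Bonferroni controls the error rate that the plan says it will control, no power is promised for any secondary endpoint, and the largest gain needs every endpoint to respond. All of that stands, and it is why the point is an optional improvement and not a correction.

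Several stronger readings are tempting, and the article does not support them.

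- **That two significance rules contradict each other.** A reader might set the general 0.05 sentence against the Bonferroni sentence. It directly follows that sentence and reads naturally as the level for the primary test and for adjusted secondary p-values; comparing 9p with 0.05 is the same as comparing p with 0.05/9. Unadjusted testing of nine independent endpoints would give a family-wise error of 1 − 0.95⁹ = 37%, or 27% at correlation 0.5, but only if the stated correction were ignored.
- **That an undefined threshold is a defect of the plan.** The divisor cannot be counted from the article. A condensed article commonly leaves the numbered list of tests to the full protocol or SAP, neither of which is shown.
- **That Holm rescues HSPB1 in atrial tissue.** If HSPB1 has the smallest p-value, Holm tests it at the same 0.05/m as Bonferroni. The article's objectives and endpoint sections also do not rank HSPB1 above the other markers.
- **That structural remodelling should become exploratory.** The article places it among the secondary endpoints. Demoting it would change the endpoint hierarchy, and the change to Holm does not need it.

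**Conclusion.** The point holds as a minor, nearly free improvement. That Holm dominates Bonferroni at the same strong family-wise 0.05 is a mathematical fact and needs no assumption about this trial. The size of the gain does need assumptions. With nine tests, 66 per arm, d = 0.5 SD and correlation 0.3, it runs from nothing (one endpoint responding) through about 2 points (three responding) to about 12 points (all nine responding). The effect size, the correlation and the count of nine are not stated in the article. The sample size and the analysis of the primary endpoint are untouched.

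**What to change.** In Statistical Analyses:

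1. Replace the Bonferroni correction with Holm's step-down procedure at family-wise 0.05 for the secondary endpoints.
2. State that 0.05 applies to the primary test and to multiplicity-adjusted secondary p-values.
3. In the same edit, name the markers and sample types that form the family, and say whether the additional proteostasis markers in Secondary Endpoints belong to it, since Tissue Analysis does not list them. If the full protocol or SAP already closes the family, align the wording with it. Structural remodelling can stay secondary.

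The cost is wording only, with no change to patients, sampling or sample size. The one statistical drawback is that Holm has no simple matching simultaneous confidence intervals. If the sponsor wants such intervals for the secondary endpoints, keeping Bonferroni is a defensible choice.

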### Randomisation and Blinding

For randomization, we consider a 1:1 allocation ratio. Stratified random sampling will take into consideration the following: age (18–60 years or 60–80 years old), sex (male and female), and indication for cardiothoracic surgery (valve disease, CABG, and concomitant valve disease + CABG). Therefore, 12 strata will be considered. A random block size of 4 will be considered.

Stabilization of atrial cardiomyocyte proteostasis appears to be an upcoming and promising therapeutic strategy to avert the AF onset. The GENIALITY trial is the first clinical study to investigate whether HSP-boosting therapy can clinically prevent the incidence of AF in patients undergoing cardiothoracic surgery. The study outcomes will also contribute to a better understanding of the HSP pathway under therapeutic intervention, fostering future investigations with GGA derivatives.

## Conclusion

Stabilization of atrial cardiomyocyte proteostasis appears to be an upcoming and promising therapeutic strategy to avert the AF onset. The GENIALITY trial is the first clinical study to investigate whether HSP- boosting therapy can clinically prevent the incidence of AF in patients undergoing cardiothoracic surgery. The study outcomes will also contribute to a better understanding of the HSP pathway under therapeutic intervention, fostering future investigations with GGA derivatives.

## Data Availability

The data underlying this article will be shared on reasonable request to the corresponding author.
